## Background

Cardiac disease is the most common cause of morbidity and mortality in the United Kingdom, costing £29 billion [1]. Much research on cardiovascular disease has focused on men, as these diseases occur at younger ages and are more severe in males, and risk factors for cardiovascular disease in women are relatively understudied. Thyroid disease is predominantly a disease of women and is increasingly being recognised as an adverse cardiac risk factor. Levothyroxine is cheap (costs 5 pence/day), safe and commonly used generic drug (prescribed to 3% of the UK population). The appropriate use of levothyroxine in SCH patients with and without heart disease has the potential to optimise management of hypothyroidism to minimise vascular risk and to improve outcomes of AMI. The myocardium and vascular endothelial tissues have receptors for thyroid hormones and are sensitive to changes in circulating thyroid hormone concentration [2]. Even minor changes in thyroid hormone concentration may impact adversely on the cardiovascular system. Importantly, both mild hypothyroidism (SCH) and hyperthyroidism have been associated with a 20 to 80% increase in vascular morbidity and mortality risk [3-7]. This has huge population significance as a vascular risk factor, since at least 10% of older women have SCH, but this is under-recognised, owing possibly to a lack of commercial exploitability. Small intervention trials of levothyroxine in SCH have shown improvement in left ventricular function, vascular endothelial function and atherogenic lipid particles [8]. SCH after an acute cardiac problem has been associated with an up to 3.6-fold increase in cardiac mortality and a 2.3-fold increase in overall death [9,10]. Following experimental coronary artery ligation in an animal model of AMI, heart failure is associated with reduced thyroid hormone receptor expression in the myocardium, leading to tissue hypothyroidism [11]. Moreover, thyroid hormone administration improves cardiac contractility, left ventricular (LV) function, and augments myocardial remodelling [12]. In addition, thyroid hormone regulates angiogenesis, cardio-protection, cardiac metabolism, and myocyte regeneration at a molecular level, changes that can reverse left ventricular remodelling by favourably improving myocyte shape and geometry of LV cavity, thus improving recovery from AMI [13].

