### Secondary outcome measures

Secondary outcome measures will include the following:Left ventricular systolic and end diastolic volumes and myocardial viability: Cardiac MR parameters of both global and segmental LV function measurements will be obtained as per standardised protocols already in place in the Newcastle MR centre using a steady state free precession or fast gradient echo technique. In addition, further scans will be obtained 15 to 20 minutes after intravenous gadolinium-chelate administration (delayed enhancement MRI). Regions of nonviable myocardial tissue will be identified as areas of increased enhancement (hyper enhancement) whereas viable tissue will have null (black) on the acquired images.Thrombus burden: The Badimon chamber is a highly reproducible clinical *ex vivo* model of thrombosis that mimics flow conditions within the coronary circulation of man [21]. The device incorporates two chambers with internal flow channels of different diameters, one simulating high-shear flow of 1690 ml/s and the other simulating low-shear flow. The internal flow channels are lined with porcine aortic tunica media - the thrombogenic substrate. After perfusion with venous blood from the patient, flowing at 10 mL min −1 for 5 min, aortic segments are fixed in 10% formalin for 72 h. Total thrombus burden is measured using validated computer-assisted planimetry using IMAGE-PRO PLUS software (Media Cybernetics, Inc., Bethesda, MD, USA). The results are the mean of the analysed sections (μm2 .mm-1). The measurements will be performed at the Clinical Research Facility (CRF), where there are professionals who have considerable experience using this technique in other high vascular risk groups.Thromboelastography (TEG™): This is a noninvasive measure for evaluating efficiency and quality of *ex vivo* thrombus formation. Quantitative measures include clotting time parameters, clot strength and clot lysis. These parameters have been validated as highly correlated with longer term cardiac outcomes in several conditions of risk [22,23]. TEG™ will be measured at the CRF, RVI, Newcastle.Endothelial function: Endothelial dysfunction is the earliest stage in the atherosclerosis disease process. In this study, endothelial function will be assessed by measuring peripheral arterial tone using a validated tool, EndoPAT™ [24]. Endothelial function assessment using the EndoPAT™ has been shown to have a high degree of correlation with coronary artery endothelial function [25], the severity and extent of coronary artery disease [26], and traditional cardiovascular risk factors [27] and is useful in predicting future cardiovascular events [28]. EndoPAT™ assessments will be performed at the Clinical Research Facility, RVI, Newcastle at baseline and at the end of the study.Platelet reactivity: The reactivity (inhibition) of platelets to anti-platelet agents such as aspirin, clopidogrel, prasugrel and ticagrelor will be quantified by the point-of-care monitor VerifyNow™ (Accumetrics, CA, USA). Arachidonic acid reactive units and P2Y12 reactive units will be recorded at baseline and at the end of the study. This test will not be carried out in individuals who take anticoagulants such as warfarin.Safety assessments: The safety of levothyroxine therapy in post-AMI patients will be assessed at each study visit by enquiry of symptoms by New York Heart Assessment (NYHA) category classification, ECG recording for rhythm disturbance and peripheral oxygen levels by pulse oximetry (at rest).QoL and depression: This will be assessed by validated tool of measuring health status, the Short Form 12 four week recall (SF-12™), a disease specific questionnaire for heart failure, the Minnesota Living With Heart Failure Questionnaire™, and the Centre for Epidemiologic Studies Depression Scale (CES-D), at baseline and at the end of the study.

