### Administration of the study drug

Participants will be randomised to either LT4 or placebo to be taken orally once daily. This will be discussed at the time of consent and will be clear in the patient information sheet. Initial starting dose of LT4 will always be 25 mcg daily. To achieve the desired target TSH levels in the LT4-treated group (target TSH levels 0.4 to 2.5 mU/L), participants will have their TSH levels checked every 4 weeks and concomitant dose of their LT4 altered by 25 mcg daily, if required. The IMP will be provided as 5 week supplies of LT4 or matching placebo (dispensed separately at each visit), packaged into appropriate individual polypropylene bottles. The label on the bottle will not indicate details of the arm of the study to which the participant has been randomised. The label will instead contain a pack number, which will be the link to the relevant dose.

Study medication will be prescribed by the PI or co-investigator at each site using a trial-specific prescription (documenting the required IMP pack number), and dispensed according to local pharmacy practice. Independent study physicians who will be unblinded will adjust study drug dose as per protocol. The relevant pharmacy will hold a corresponding list allowing the pharmacy staff to correlate the IMP pack number with relevant packaged IMP dose for any particular IMP bottle, thus maintaining the double-blind.

Participants will be informed of potential adverse reactions and advised to contact the relevant study team if required. A study-specific participant contact card will also be provided.

Once randomised, the participant will begin their study medication on Day 0.

At 4, 8, 12 and 24 weeks (+/− 7 days), serum TSH levels will be checked and LT4 doses adjusted as follows (the next bottle of IMP should be started at week 4, 8, 12, 24 +/− 7 days, respectively):

LT4 group:TSH 0.4 to 2.5 mU/L: Continue LT4 at current dose once dailyTSH > 2.5 mU/L: LT4 increased by 25 mcg dailyTSH < 0.4 mU/L: LT4 reduced by 25 mcg, or if already on 25 mcg daily (the lowest possible dose), then recheck TFTs in 4 weeks. If TSH is ≥0.4 mU/L then continue on current dose. Otherwise, if TSH continues to be <0.4 mU/L on the repeat blood test, then the participant will be withdrawn from the study.

Placebo group:Individuals in this group will have a fresh bottle of IMP starting at 4, 8, 12, 24 +/− 7 days after blood tests to maintain the double blind.

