LT4 treatment based on the above regimen will continue for a total of approximately 52 weeks at which point the final set of study specific assessments will be made (with a further follow-up phone call at approximately 53 weeks). If a participant in the placebo arm has a TSH >10 mU/L then their TFTs will be rechecked in 4 weeks. If, the TSH is ≤10 mU/L on the repeat test then the participant will continue with the study and, if, the TSH continues to be >10 mU/L then the participant will be withdrawn from the study. At the final visit, participants on each arm of the study will stop their IMP and will be referred back to their GP to have their thyroid function checked in 6 to 12 weeks. The GP and the patient will be encouraged to discuss whether there is a need to commence LT4 therapy in these individuals based on the clinical situation. The GP letter (sent once the participant is randomised) and the GP follow-up letter (sent after each participant completes their IMP) outlines the suggestion to recheck TSH levels at 6to 12 weeks for each participant once they have completed their IMP.

At the end of each visit, participants will be asked to return any surplus study drug in the original packaging to the study team, who will verify and document compliance. All unused study medication and packaging will be sent to the local pharmacy for documentation and destruction as per local policy (following appropriate reconciliation by the Trial Manager). Documentation of prescribing, dispensing and return of study medication shall be maintained for study records.

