**Table 1 Tab1:** **Schedule of events for ThyrAMI 2**

	**Pre-screening**	**Baseline**			**Randomisation**	**follow-up**							
**VISIT**		**1A**	**1B**	**1C**		**2**	**3**	**4**	**5**	**6A**	**6B**	**6C**	**7**
**assessments**	**Within 24 hours of AMI**	**7 to 10 days post AMI**	**Day 0**			**Week 4 (+/− 7 days)**	**Week 8 (+/− 7 days)**	**Week 12 (+/− 7 days)**	**Week 24 (+/− 7 days)**	**Week 52 (+/− 7 days)**			**Week 53 (+/− 7 days)**
Identification and initial approach (including provision of PIS)	X												
Eligibility criteria checked	X												
Written informed consentǂ		X											
Physical examination (height ****, weight, BP, pulse)		X										X	
Venepuncture		X*				X**	X**	X**	X**			X*	
Clinical history (medical history, medication list)		X											
Questionnaires (SF12, MLWHFQ, CES-D) completed		X										X	
Safety checks (ECG, pulse oximetry and NYHA assessment		X				X	X	X	X			X	
Cardiac MRI			X							X			
EndoPat, Badimon chamber, VerifyNow and TEG analysis				X							X		
Randomisation (after written informed consent obtained) and study drug dispensation					X ***#***								
Study medication prescribed and dispensed (following LT4 dose assessment at visits 2 to 5 only)						X	X	X	X				
Study medication compliance checks						X	X	X	X			X	
Concomitant medication						X	X	X	X			X	
Adverse events						X	X	X	X			X	X
Serious adverse events						X	X	X	X			X	X

X* 20 ml blood: TSH, FT4, FT3, TPO antibodies, Total cholesterol, HDL, Triglycerides, serum BNP, endothelial markers (10 ml gel/gold tube and 10 ml EDTA/purple tube).

X** 5 ml blood: TSH, FT4, FT3 only (gel/gold tube).

Height ****: To be measured at baseline visit only (or could be self-reported if apparatus not available; for example at participant’s home).

ǂ After full discussion and answering any questions.

List of Abbreviations:

BP, blood pressure; BTF, British Thyroid Foundation; CES-D, Centre for Epidemiologic Studies Depression Scale; ECG, electrocardiogram; LT4, levothyroxine; MLWHFQ, Minnesota Living With Heart Failure Questionnaire; MRI, magnetic resonance imaging; NYHA, New York Heart Association; PIS, patient information sheet(s); SF12, short-form health survey; TEG, thromboelastography.

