### Withdrawal of participants

Participants have the right to withdraw from the study at any time for any reason without giving a reason. The investigator also has the right to withdraw patients from the study drug in the event of inter-current illness, adverse events, serious adverse events, suspected unexpected serious adverse reactions, protocol violations, administrative reasons or other reasons.

Should a participant decide to withdraw from the study, their wishes will be respected. These participants will be asked to complete a “confirmation of withdrawal” form to document their decision. However, for participants that withdraw due to reasons other than related to tolerance of MR scanning, they would be offered the chance to have the primary outcome assessment (cardiac MR imaging) performed at the time of withdrawal.

Participants who have serum TSH <0.4 or >10.0 mU/L on two separate occasions at least 4 weeks apart whilst on study drug will be withdrawn from the study due to safety reasons. For study participants who withdraw from the study, a replacement eligible participant will be recruited, if the study is still recruiting.

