### Pharmacovigilance

The safety of LT4 in this study will be evaluated by examining the occurrences of all adverse events, adverse drug reactions, unexpected adverse reactions, serious adverse reactions or suspected unexpected serious adverse reactions as defined by the Medicines for Human Use (Clinical Trials) Regulations [35]. The relationship and expectedness of the adverse event or reaction (causality) will be assessed by the site investigator and relayed to the chief investigator who, on behalf of the sponsor (Gateshead Health NHS Foundation Trust), will notify the regulatory bodies, the Medicines and the Healthcare Products Regulatory Agency (MHRA) and the research ethics committee (REC), within 7 days for fatal and life-threatening events and 15 days for non-life-threatening events. All study investigators will be notified.

Most adverse events and adverse drug reactions that occur in this study, whether they are serious or not, will be expected treatment-related toxicities due to the drugs used in this study. For a full list of expected undesirable effects of Levothyroxine, please refer to the relevant Summaries of Product Characteristics [29,30].

We do not anticipate adverse effects of LT4. Nevertheless, safety of participants is of paramount importance, and therefore, LT4 dose will be commenced at a small dose (25 mcg daily) and the dose increased every 4 weeks by 25 mcg daily until the serum TSH is within the required range. Safety measures (ECG, symptoms of heart failure, and pulse oximetry) will be assessed at visits 2 to 6. If severe hypothyroidism develops (TSH >10 mU/L with low FT4 levels), then symptoms including fatigue, weight gain and poor memory may develop. For such individuals, we will recheck TFT in 7 days. If serum TSH remains above 10 mU/L, then such patients will be withdrawn from the study. In addition, we will assess the health of participants via a health status questionnaire. Participants will also be provided with a helpline number in case they experience any problems.

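### TSH is said to be checked every 4 weeks, but the itemised visits leave about 28 weeks without a check after a permitted dose increase at week 24, so the two-value TSH withdrawal rule cannot act on values that first leave range in that period

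*Protocol article*

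**What the plan says.** All references are to the ThyrAMI 2 part of the protocol article.

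**Monitoring described as 4-weekly.** Administration of the study drug states that "participants will have their TSH levels checked every 4 weeks and concomitant dose of their LT4 altered by 25 mcg daily, if required". Pharmacovigilance describes titration in the same way, with "the dose increased every 4 weeks by 25 mcg daily until the serum TSH is within the required range".

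**Monitoring as itemised.** Later in the same administration section: "At 4, 8, 12 and 24 weeks (+/− 7 days), serum TSH levels will be checked and LT4 doses adjusted as follows". The rules that follow raise the dose by 25 mcg when TSH exceeds 2.5 mU/L and lower it by 25 mcg when TSH is below 0.4 mU/L. New bottles start at the same four time points. Table 1 places follow-up blood samples at weeks 4, 8, 12, 24 and 52, with no visit between the last two, and limits dose assessment to visits 2 to 5.

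**End of treatment.** "LT4 treatment based on the above regimen will continue for a total of approximately 52 weeks", and study drug stops in both arms at the final visit.

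**The safety rule.** Under Withdrawal of participants, those with TSH below 0.4 or above 10.0 mU/L "on two separate occasions at least 4 weeks apart whilst on study drug will be withdrawn from the study due to safety reasons".

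**Rechecks outside the schedule.** There are three:
- at 4 weeks, when TSH is below 0.4 mU/L on 25 mcg;
- at 4 weeks, when TSH exceeds 10 mU/L on placebo;
- at 7 days, when TSH exceeds 10 mU/L with low FT4 (Pharmacovigilance).

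**The safety outcome.** Secondary outcome measures states: "The safety of levothyroxine therapy in post-AMI patients will be assessed at each study visit by enquiry of symptoms". It then lists NYHA class, ECG and pulse oximetry. Pharmacovigilance adds adverse events and reactions. Neither names an out-of-range TSH.

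**The concern.** A rule that needs two on-drug values can work only if the schedule supplies a second value in time. The itemised schedule is densest early and sparsest after the last dose step, and that step may be an increase. A participant whose TSH falls below 0.4 mU/L on the week-24 dose would stay on that dose until the end of treatment, with nothing scheduled to reveal it.

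The protocol gives its own reasons for caring. Safety after AMI is part of the stated objective, and the Background says that "both mild hypothyroidism (SCH) and hyperthyroidism have been associated with a 20 to 80% increase in vascular morbidity and mortality risk". The data monitoring committee is set up mainly to follow safety endpoints. The 52-week LVEF comparison would also be read with no scheduled information on whether TSH stayed within 0.4 to 2.5 mU/L between weeks 24 and 52.

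The contradiction adds a practical problem. A site following the 4-weekly sentence and a site following Table 1 would run different monitoring, and both could claim to follow the protocol.

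**Working it through.** The plan states no figure to reproduce here. The check is interval arithmetic on the schedule, followed by a case-by-case reading of the rules.

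**Inputs.** Itemised TSH checks: weeks 4, 8, 12 and 24 (administration section) and week 52 (Table 1), each ±7 days. Treatment length: about 52 weeks. Rule: two values out of range, at least 4 weeks apart, on drug.

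**Step 1: gaps between checks, from week 0.**
4 − 0 = 4; 8 − 4 = 4; 12 − 8 = 4; 24 − 12 = 12; 52 − 24 = 28 weeks.
With windows of ±1 week at each end, the last gap is 28 ± 2, that is 26 to 30 weeks.
Share of treatment: 28/52 = 0.538, or 54%.

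**Step 2: what a 4-weekly schedule would contain.** It would add checks at weeks 16 and 20, and at 28, 32, 36, 40, 44 and 48. None of these eight is in Table 1. The two 4-weekly statements also differ from each other. The Pharmacovigilance sentence runs only until TSH is in range. It would imply a check at about week 28 for someone whose dose is raised at week 24, but none for someone in range at week 24. Only the unqualified sentence in the administration section covers both.

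**Step 3: can the two-value rule act before week 52 on the itemised schedule?**

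| Situation | What the text supplies | Can the rule act before week 52? |
|---|---|---|
| Out of range at weeks 12 and 24 | Two values, 12 weeks apart | Yes, at week 24 |
| First <0.4 at week 24, on 25 mcg | Recheck at about 24 + 4 = week 28 | Yes |
| First <0.4 at week 24, on more than 25 mcg | Dose reduced; no recheck itemised | No, but the first value has been acted on |
| First >10 at week 24, placebo | Recheck at about week 28 | Yes |
| First >10 at week 24, levothyroxine | Dose increased; no 4-week recheck itemised (7-day recheck if FT4 is low) | Not under the two-value rule |
| First <0.4 or >10 after week 24, either arm, with or without a week-24 dose change | One value, at week 52 | No |

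In the last row, a confirmatory value at least 4 weeks later would fall at week 52 + 4 = 56 or after, when the drug has been stopped. The unscheduled rechecks do not help, because each needs a first abnormal value to trigger it and none is scheduled between weeks 24 and 52.

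**The case against.** The strongest reply is that the gap may not exist. If the 4-weekly sentence governs, a week-24 increase is followed by a check at about week 28 and the rule works. That is a fair reading of one sentence, but the weekly list, the bottle-start weeks and Table 1 all follow the sparse schedule, and Table 1 is what sites are likely to run. The reply therefore confirms the contradiction and does not remove it.

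It can also be said that overtreatment visible at week 24 is handled. That stands: low TSH at that visit leads to a dose reduction or, on 25 mcg, a 4-week recheck. A reader might infer that the rule is inoperative for everyone throughout the last 28 weeks. The text does not support that; the failure concerns values that first leave range after week 24, with the narrower week-24 cases shown in the table.

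A reader might further infer that the safety comparison is biased in favour of levothyroxine. The documents do not show this. Serious adverse events are recorded throughout treatment. Adverse events, ECG, NYHA class and oximetry are collected at week 52 in both arms, and adverse events again at week 53. Participants also have a contact card and a helpline. What goes unseen is the laboratory abnormality itself, and even that is measured once, at week 52.

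Finally, listing TSH excursions by visit and arm is ordinary analysis-plan content, so its absence from the article is not a fault. How often to monitor is a clinical choice for the sponsor. Both points stand, and the fix respects them.

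**Conclusion.** The concern holds in a limited form. The firm defect is documentary: the statements of 4-weekly TSH checks and titration cannot be squared with the itemised list and Table 1. On the itemised schedule it has a concrete consequence. For about 28 weeks (26 to 30), or 54% of treatment, and directly after a visit at which the dose may be raised, TSH that first goes below 0.4 or above 10 mU/L cannot trigger the stated withdrawal rule. Biochemical overtreatment in that period goes unseen until the drug is stopped.

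This rests on two assumptions: that sites follow Table 1, and that participants take study drug to week 52 as the protocol states. It needs no assumption about how many doses change.

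A reader may want a count of affected participants. The document gives neither the share whose dose would change at week 24 nor how often a 25 mcg step would take TSH below 0.4 mU/L, so no count is offered. The planned primary LVEF analysis is not invalidated. The matter should be corrected because it concerns a safety rule in post-AMI patients.

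**What to change.** 1. Reconcile four places: Administration of the study drug (every 4 weeks versus weeks 4, 8, 12 and 24), Table 1 (next TSH after week 24 at week 52), Withdrawal of participants (two on-drug values at least 4 weeks apart) and Pharmacovigilance (4-weekly titration until in range). After the change, all four should describe one schedule, under which the stated TSH rule can operate after the last permitted dose change. Which schedule or rule achieves this is for the sponsor to decide.
2. As a lesser addition, report the proportions with TSH below 0.4 and above 10 mU/L by randomised arm at each scheduled visit, including the single week-52 value. The analysis plan is a suitable place for this.

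Cost: the first item is a wording amendment. Depending on the sponsor's choice, it may mean additional 5 ml thyroid samples for some participants; the protocol already uses unscheduled rechecks elsewhere. The second is one table from samples already planned.
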